## Management of Intercurrent Medications

Participants who begin taking any medication during the trial that is listed as an exclusionary medication at screening will temporarily discontinue study drug. Study drug may be resumed if no exclusionary medication has been taken in the last 4 weeks, serum creatinine is within 0.3 mg/dL of enrollment level, and a rapid test for HIV antibodies is negative.

## HIV and Hepatitis B

Participants who are identified as infected with HIV and/or hepatitis B will permanently discontinue study drug and be provided linkages to care.

## Clinical Management of Pregnancy

All female study participants are required to be using an effective method of contraception according to section 5.3, and intending to use this method for the duration of study participation. Study staff will provide contraceptive counseling to enrolled female participants as needed throughout the duration of study participation and will facilitate access to contraceptive services through referrals to local service providers. Study staff will also provide all participants with male and/or female condoms and counseling on use of condoms during study participation.

Pregnancy testing will be performed at all study visits for female participants, and participants will be encouraged to report all signs or symptoms of pregnancy to study staff. Participants who become pregnant during the course of the study will permanently discontinue study drug. The principal investigator or clinician will counsel any participant who becomes pregnant regarding possible risks to the fetus and refer the participant to all applicable services; however, sites will not be responsible for paying for pregnancy-related care.

Participants who are pregnant at the termination visit will continue to be followed through phone contact with study staff until the pregnancy outcome is ascertained (or the investigator team determines that the pregnancy outcome cannot be ascertained). Pregnancy outcomes will be reported on relevant case report forms.

## Social AEs

Participation in the study could lead to social harms that may include loss of privacy or stigmatization. Information regarding social harms will be collected during follow-up visits and will be recorded in log form. All social harms will be brought to the attention of the medical officer who will determine appropriate follow-up.

## Review of AEs

The principal investigator will serve as the medical officer for this trial and review all laboratory and clinical adverse events weekly. As described in section 9.3, all SAEs, grade 3 or higher AEs, and creatinine elevations ≥ 0.5 mg/dL over baseline will be reported to the medical officer within 72 hours. The principal investigator will meet with appropriate members of the investigator team on a monthly basis to discuss enrollment, retention, and safety of study participants.

# DATA MANAGEMENT AND STATISTICAL CONSIDERATIONS

This is a three-period, open label, single-site crossover study. All enrolled participants will undergo 3 dosing regimens. The sequence of these dosing regimens will be randomly assigned. The total length of follow-up is approximately 36 weeks (18 weeks on study drug).

## Study Primary Endpoint and Predictor Variables

Consistent with the primary study objectives, the following primary endpoint will be assessed:

- Tenofovir hair concentration: Tenofovir hair levels will be determined from a specimen containing 150-200 hairs collected at enrollment and on the last day of each period. For each participant, absolute hair levels and ratios of hair levels between conditions (7 vs. 4 doses/week, 4 vs. 2 doses/week, and 7 vs.2 dose/week) will be determined.

The following will be primary predictor variables:

- Dosing condition: The dosing condition will be examined as an ordinal variable: 2, 4, and 7 doses/week. We will also use actual percentage of total doses (by directly observed recorded doses and self-administered recorded doses) taken over the 6 week period as a continuous predictor of hair levels.
- PK parameters: The primary predictor variable of total exposure (PK contribution) will be oral clearance (CL/F). This variable is estimated by the equation “dose/AUC,” where AUC is the area under the plasma-concentration time curve for each intensive PK sampling procedure. Other parameters of drug exposure that will be evaluated as predictor variables include the concentration at the end of the dosing interval (trough or C_min_), peak plasma level (C_max_), and AUC alone. These PK variables will be calculated using non-compartmental methods.

## Study Hypotheses

The study hypotheses for the primary objectives are:

- Tenofovir hair levels will correlate highly with frequency of tenofovir dosing. We expect hair levels from the 7 doses/week condition will exceed hair levels for the 2 doses/week condition. In addition, we expect that few doses from the 4 doses/week condition will exceed hair levels observed in the 7 doses/week condition, and few hair levels from the 2 doses/week condition will exceed hair levels observed in the 4 doses/week condition.
- Decreased oral clearance (CL/F) and higher AUC, C_min_, and C_max_ values will be associated with higher absolute TFV hair levels and an increased ratio of TFV hair concentrations between doses.

## Biostatistical Methods

Analyses for all aims will include initial examination of summary statistics and graphical summaries of data, checking of model assumptions, and careful examination of estimates and their confidence intervals rather than exclusive attention to p-values. When parametric assumptions are violated, nonparametric alternatives will be evaluated. Because multivariate modeling and controlling for potential confounders are difficult with nonparametric methods, bootstrapping strategies will also be considered for obtaining valid p-values and confidence intervals for parametric models whose assumptions are violated. This approach also has the advantage of providing estimates and confidence intervals, which are often unavailable with nonparametric methods. Over-interpretation of isolated or implausible findings of nominal statistical significance will be avoided by examination of corresponding estimates and confidence intervals and of related results while taking account of the scientific context and relationships among analyses (rather than by formal multiple comparisons adjustments).

The primary parameters of interest in this study will be TFV hair concentration under each dosing condition. We will determine mean, median, and 95% confidence intervals for this parameter for each dosing condition being tested. We will then estimate ratios of TFV levels in hair of different pair-wise combinations of dosing conditions and determine mean, geometric mean, median, and 95% confidence intervals for these ratios. We will also assess the ability of hair levels to discriminate between conditions, in particular noting how often any level under 4 day/week dosing exceeds any level observed under 100% adherence, and how often any level under 2 day/week dosing exceeds any level observed under 4 day/week or 7 day/week dosing.

We will first use scatterplots with LOWESS smooths to examine the relationships between TFV hair concentration and PK parameters calculated from the intensive pharmacokinetic studies, as well as the relationships between dose and hair concentration stratified by PK values. These PK parameters include clearance (CL/F) as estimated by dose/AUC, C_min_ or trough level, C_max_ or peak level, t_max_ or time to reach peak levels, and area-under-the-curve (AUC). Linear and possibly non-linear mixed models for TFV levels in hair will be used to assess these relationships. Random effects for participant will be used to account for within-subject correlation and thus capture the efficiency gains afforded by the crossover design. Outcomes will be normalized as necessary to meet model assumptions, and bootstrap confidence intervals computed as a sensitivity check. With log-transformed TFV hair levels as the outcome, effect estimates for both dose and PK variables will be interpretable in terms of percentage effects on TFV hair concentration. We will first estimate the overall effect of PK variables on TFV hair levels, carefully considering non-linear relationships and if necessary using non-linear mixed models. For example, we expect that lower clearance and higher AUCs will be associated with higher hair levels. In addition, we will examine modification of the associations between dose and hair concentrations by PK variables; in particular, we hypothesize that hair concentration will increase more rapidly across the 3 dose levels in participants with lower clearance and higher AUC.

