# PROTOCOL SUMMARY

**Protocol title:** Phase 1 Pharmacokinetic Study of Varying Dosing Patterns on Tenofovir Hair Concentrations

**Clinical Phase:** 1

**Protocol Chair:** [name], MPH

**Sample Size:** 24

**Trial Site:** University of California, San Francisco; San Francisco Department of Public Health

**Study Population:** Healthy, HIV-uninfected men and women age 18 or older

**Study Design:** Phase 1, open-label, randomized, six sequence, three period, single-site cross-over study

**Study Duration:**  Approximately 20-36 weeks per participant (18 weeks on study drug)

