## Dispensing and Dosing

Study participants will receive study drug using modified directly observed therapy (mDOT) conducted by a research associate (RA) trained in mDOT procedures. Study product will be dispensed to enrolled participants, upon receipt of a written prescription from an authorized prescriber. Participants will be randomized to one of six study regimen sequences (see section 7.5). Each participant’s study sequence will consist of three dosing periods of 6 weeks each, with a break of at least 3 weeks between dosing periods. For UCSF students, each study period will occur during an academic quarter, with a break between dosing periods of several weeks corresponding to the vacation breaks between quarters. The total study duration will be approximately five or more months for non-students, and approximately 36 weeks for UCSF students. Participants will take pills according to the dosing schedule designated by their randomized sequence (see section 7.5 for details) and meet with study staff for mDOT as described below (see section 7.8). Dosing times will be recorded by the study staff for the directly observed and telephone mDOT doses in a dosing log. Participants will be provided a one-week pre-packed emergency supply of medication to be used if they cannot or fail to make a scheduled visit with the study staff. Study drug may be taken without regard to meals.

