## Enrollment

At the enrollment visit, the participant’s laboratory results will be reviewed with the study participant. Another rapid HIV test will be performed. All eligibility criteria will be reviewed and confirmed. If the participant is eligible, he or she will be enrolled and randomly assigned into one of 6 arms of this 3 condition cross-over study (see section 7.5). Each arm will be stratified by gender. The 4 doses/week group will occur on Monday, Tuesday, Thursday, and Friday, and the 2 doses/week will occur on Tuesdays and Wednesdays. Enrollments may be scheduled on any day of the week, but study drug initiation will occur at the beginning of the week (Monday for the 4 and 7 doses/week groups and Tuesday for the 2 doses/week group).

Blood, hair, and urine specimens will be collected at the enrollment visit. Participants will receive a detailed daily dosing schedule and visit calendar for all 3 periods of their study participation. The participants’ cell phone number, other phone numbers and a list of places where they might be located will be obtained along with a follow-up plan in the event that the participant is not at the designated meeting place.  A one-week supply of back-up medication will be provided in the event that participants are unable to be seen for directly observed doses. Study participants will be provided access to a 24 hour, 7 days/week emergency pager to discuss any potential study related adverse events with a study clinician.

| **Enrollment Visit** | |
| --- | --- |
| Component | Procedure/Analysis |
| Administrative | - Assign Participant ID or Screen failure ID - Review/update locator information - Provide lab results to participant - Confirm eligibility - Follow procedures for randomization assignment - Explain mDOT procedures - Confirm cell-phone number for doses observed by phone and reminder text messages - Provide dosing schedule and visit calendar to participant - Schedule next study visit with RA - Provide reimbursement for visit |
| Clinical | - Update medical history - Update list of concomitant medications - Perform full physical exam - Provide counseling   - HIV pre- and post-test counseling |
| Urine | - Collect urine sample   - Qualitative hCG   - Dipstick UA (and full UA with microscopy if greater than trace protein, glucose, heme, or leukocytes) |

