## Randomization

The study statistician will randomize allocation sequences in two blocks of 6 within each gender stratum, (12 male and 12 female study participants). Each study participant will be randomly assigned to 1 of the 6 dosing sequences based on order of enrollment. Assignments will be concealed in sequentially numbered, opaque, sealed envelopes. Participants will be randomized to a sequence only after they have consented to participate, met eligibility criteria, and enrolled in the study.

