## Sample Size

This study will provide the first information on how frequency of dosing influences hair levels of tenofovir, so there is no preliminary data on the person-to-person variability in hair level ratios between conditions. Primary interest will focus on describing typical ratios and their variability, as well as on a preliminary assessment of how well hair levels can distinguish 100% adherence from partial adherence. With 24 subjects and a mix of both sexes, little or no overlap between the distributions of hair levels under different conditions would strongly suggest substantial potential utility of hair levels for explaining breakthrough HIV infections in prevention studies.

There is no preliminary data on the within-person correlation of hair concentration levels, on which to base formal power calculations for the mixed model. However, for hair concentration to be a useful surrogate, it will need to be reliable – that is, highly correlated within-subjects – and very strongly associated with PK variables and dose. The proposed mixed models will provide preliminary estimates of the within-subject correlation of TFV hair levels, as well as estimates of the strength of the associations between hair concentration, dose, and PK variables.

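### The ratio summaries and the named mixed-model terms leave out period and preceding regimen, although the balanced six-sequence layout can estimate both

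*Protocol*

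**What the plan says.** The Protocol Summary describes a "Phase 1, open-label, randomized, six sequence, three period, single-site cross-over study". Section 7.5 uses all six orders of the 7, 4 and 2 doses/week regimens, with four participants each (two men, two women). Section 7.6 has the statistician "randomize allocation sequences in two blocks of 6 within each gender stratum".

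Section 10.3 makes hair level under each regimen the main parameter and continues: "We will then estimate ratios of TFV levels in hair of different pair-wise combinations of dosing conditions and determine mean, geometric mean, median", with 95% confidence intervals. It then counts how often levels under one regimen exceed levels under a higher one. Neither summary carries an adjustment. The mixed models are described for the relation of hair level to PK and dose, with this statement on structure: "Random effects for participant will be used to account for within-subject correlation and thus capture the efficiency gains afforded by the crossover design". The effects it names are dose, PK variables and modification of the dose effect by PK.

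No part of Section 10 names period, sequence or preceding regimen. Section 10.4 says that interest lies mainly in typical ratios and how much they vary, and in how well hair levels separate full from partial adherence.

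On timing, Section 6.2 sets "three dosing periods of 6 weeks each, with a break of at least 3 weeks between dosing periods". Section 3.1 says that drug enters hair over a span of weeks up to months. Sections 7.1 and 8.6 place hair collection at enrollment and at the end of each period only.

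**The concern.** A person's ratio of two regimens also compares two calendar periods and two different preceding regimens. A raw ratio cannot separate these. If hair level drifts over the study, the drift enters each person's ratio with a sign that depends on the sequence, so ratios look more variable than they are.

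If drug from one period remains in the sample taken at the end of the next, the effect is directional. No regimen follows itself, so in periods B and C the 2 doses/week regimen always follows a higher one and the 7 doses/week regimen always a lower one. Retained drug therefore lowers the average ratios and adds overlap between regimens, and Section 10.4 uses little or no overlap as its sign of the assay's usefulness.

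**Working it through.** **Plan's own figure.** The sample size of 24 is not derived from power, and Section 10.4 says no data existed for that. The allocation is consistent: 6 sequences × 4 = 24, and 2 blocks × 6 × 2 sexes = 24.

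**Can the design estimate the missing terms?** Each regimen occurs in each period in 8 participants, and each ordered pair of consecutive regimens occurs in 8 participants. The table shows least squares on the 72 observations with participant effects, where σ is the within-person residual SD on the log scale.

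| Terms besides participant and regimen | Parameters | Residual df | Variance of a regimen contrast |
|---|---|---|---|
| none | 26 | 46 | 2σ²/24 = 0.0833 σ² |
| period | 28 | 44 | 0.0833 σ² |
| period and preceding regimen | 30 | 42 | 0.1042 σ² |

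Period costs two degrees of freedom and no variance. Preceding regimen raises the variance by 0.1042/0.0833 = 1.25, and the standard error by √1.25 = 1.12. A preceding-regimen factor with the levels none, 2, 4 and 7 would be aliased beside period, because "none" is period A (31 columns, rank 30). Only two of its degrees of freedom are estimable.

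**Period effect (size assumed).** Let the log hair level drift by δ per period. Over sequences 1 to 6, the position of 7 doses/week minus the position of 2 doses/week is −2, −1, −1, 1, 1, 2.
- The mean is 0, so there is no bias with all 24 complete.
- The mean square is (4+1+1+1+1+4)/6 = 2, so the log-ratio variance is 2σ² + 2δ² and the interval widens by √(1 + δ²/σ²).
- At σ = 0.25, δ = 0.1 gives √1.16 = 1.08 and δ = 0.2 gives √1.64 = 1.28.
- For δ of 0.1 to 0.2 and σ of 0.15 to 0.35, the widening runs from 4% to 67%.
- Dropout: with levels rising by a factor of 1.2 per period, losing 2 participants from sequence 6 multiplies the 7:2 ratio by 1.2^(−4/22) = 0.967. Losing all 4 gives 1.2^(−8/20) = 0.930.

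**Carryover (size assumed).** Take levels proportional to dose plus a fraction c of the preceding regimen's level. At c = 0.2 the 7:2 ratios over sequences 1 to 6 are 7/2.8, 7/3.4, 7.8/3.4, 7.4/2.8, 7.4/2 and 7.8/2. Their geometric mean is 2.77, against a true 3.50.

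| c | 7:2 raw (true 3.50) | 7:2 with preceding-regimen terms | 4:2 raw (true 2.00) | 4:2 with terms |
|---|---|---|---|---|
| 0.1 | 3.06 | 3.21 | 1.83 | 1.85 |
| 0.2 | 2.77 | 3.01 | 1.71 | 1.75 |
| 0.5 | 2.25 | 2.64 | 1.51 | 1.58 |

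When carryover adds in ng/mg, as here, the log-scale terms remove about 35% of the log bias for 7:2, 12–18% for 4:2 and 68–85% for 7:4. They remove all of it only if carryover is additive on the log scale. A period term alone removes none of it.

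**Overlap.** With assumed log SDs of 0.3 between and 0.2 within persons, the share of pairs in which a 2 doses/week level exceeds a 4 doses/week level rises from 8% without carryover to 12% at c = 0.1 and 17% at c = 0.2.

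**Period A alone.** There are 8 participants per regimen and no carryover. With the same SDs, the standard error is √(0.09 + 0.04) × √(2/8) = 0.18. The 95% limits are about ×/÷ 1.45 (t on 21 df, pooled over three groups).

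**The case against.** The covariate list in Section 10.3 is not closed. The section speaks in general terms of controlling for confounders, and exact model terms are often left to a statistical analysis plan. That stands: a reader might infer that period is excluded from the model, and the text does not say so. It does not rescue the ratio and overlap summaries, which the protocol itself chooses and which cannot absorb order effects.

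Assay drift is an unlikely source of a period effect. Section 8.6 runs all samples in one batch after collection ends, with laboratory staff blinded to regimen. This stands too, and leaves only drift arising in the participants or their hair.

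A reader might also infer that omitting sex harms the primary ratios, because sex is a randomisation stratum. It does not: a sex main effect cancels within each person, and stratified randomisation, not the six sequences, deals with sex. Sex matters for absolute levels, overlap and between-person PK associations.

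Finally, one might want the carryover-adjusted model as the primary analysis. The calculation does not support that: it costs 25% in variance and leaves most of the 7:2 and 4:2 bias if carryover adds in ng/mg. The period A check is also weak, since limits of ×/÷ 1.45 cannot separate 3.06 from 3.50, a factor of 1.14.

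**Conclusion.** The point holds in limited form. As written, the ratios and overlap counts are unadjusted, and neither period nor preceding regimen is named for the model, although the layout can estimate both.

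Ignoring period does not bias the mean log ratio while all 24 are complete. It overstates the variability of the ratios and widens their intervals, by 8% or 28% in the central examples. Bias arises if dropout is uneven, which is possible because Section 7.12 leaves replacement to discretion.

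Carryover is plausible, given slow uptake into hair, a break that may last only 3 weeks, and no hair sample at the start of periods B and C. The documents do not show that it occurs or how large it is. It would be wrong to read the plan as producing ratios known to be biased. The values of δ, σ, c and the two SDs are all assumptions used to show scale.

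**What to change.** In Section 10.3, make the primary estimates of the three geometric mean ratios, with 95% confidence intervals, the regimen contrasts from one mixed model on log hair level. Use fixed effects for regimen and period and a random participant effect. Keep the raw ratios and overlap counts as description.

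Add two sensitivity analyses:
- The same model with first-order preceding-regimen terms, coded with two degrees of freedom beside period. State that the correction is partial if carryover adds in ng/mg, and least for 4:2.
- Ratios and overlap from period A alone, described as free of carryover but imprecise.

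Include sex in the models of absolute hair level and of between-person PK terms. It is not needed for the within-person ratios.

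The cost is analysis wording only, with no change to sample size, visits or specimens. The period term takes two degrees of freedom and no variance in the complete design. The preceding-regimen model costs 25% in variance (12% in standard error), which is why it stays a sensitivity analysis.
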